### Blinding

2.4

It is not possible to blind participants or researchers to conditions as all will know whether they will be using the smartphone application or not. Participants are, however, unaware of the content of the application or the study's hypotheses.

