### Design

2.1

The effectiveness of the intervention will be examined by means of a Randomized Controlled Trial (RCT) with two conditions: 1) a smartphone-based intervention condition, and 2) an active control condition. In the smartphone condition, participants receive the intervention over a period of three weeks. In the control condition, participants actively set goals, but will receive no further intervention.

All participants start with an individual intake session with a member of the research team in the lab at the university. During this session participants provide active informed consent, set goals for the coming month (i.e., monthly goal) and the year (i.e., yearly goal), and complete a series of questionnaires (baseline assessment). In addition, participants in the smartphone condition will take a photo of their face (a ‘selfie’) for avatar creation and install the application on their phone.

Assessments will be conducted prior, during, and immediately after the intervention, and at 3-month follow-up. Participants in the control condition will complete the assessments at parallel points in time. The outcomes will be assessed using online questionnaires (using Qualtrics software) completed by the participants. Academic results will be requested from the university at the end of the academic year after participants' consent. The interim assessments (one week and two weeks after baseline assessment) concern a subset of the outcomes. In exchange for participation, participants receive €25,- or 6 course credits after completion of the post-measurement, and an additional €10,- for completion of the 3-month follow-up (see Fig. 1 for the study flow chart).

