### Recruitment and randomization

2.3

Participants will be recruited via the university's official communication channels (e.g., university website, social media). Additionally, flyers will be distributed in university buildings. Furthermore, student associations will be requested to distribute the study advertisement among their members. Finally, the study will be advertised during the university's introduction week for incoming students, and announced at lectures for first-year students.

Interested students can schedule an appointment for the intake session. At the beginning of the session, students are screened for eligibility. Eligible students are randomly assigned to one of the two conditions on a 1:1 ratio, using block randomization with blocks of 6 (i.e., within a block 3 participants are allocated to each condition), and proceed with the intake session.

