### Data management

2.7

All members of the research team have signed a confidentiality statement, are familiar with procedure to manage and store data (in line with the guidelines and procedures of the Ethics Board of the Institute of Education and Child Studies at Leiden University (ECWP2021-320)), and have access to the data. Data is collected online and will be stored on secured servers of Leiden University that are backed up regularly. To monitor data quality, attention checks will be incorporated in the questionnaires.

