### Statistical analyses

2.8

Data will be analyzed on the basis of an intention-to-treat principle, meaning that participants will be included in the analyses regardless of whether they received the (complete) intervention or not. Depending on the analytical model, missing data will be handled either with Multiple Imputation (MI) or with Full Information Maximum Likelihood (FIML). Conditions will be compared at baseline to examine initial differences on age and gender. In case of differences between conditions, these variables will be controlled for in subsequent analyses.

Users' experiences and adherence to the intervention (aim 1) will be examined through the examination of usage data and user experience measures. The overall effectiveness of the intervention (aim 2) will be examined by comparing conditions on the primary and secondary outcomes (except for personality) using Analysis of Covariance (ANCOVA), with the baseline measure of the relevant outcome as covariate, and Latent Growth Curve (LGC) modeling. This enables us to examine differences between conditions immediately after the intervention and whether trajectories of change differ between conditions. To examine participants' change after each intervention module (aim 3), we will conduct repeated measures ANOVAs on the outcomes that are measured on a weekly basis, i.e., self-defeating behavior, future self-identification, and psychosocial wellbeing.

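### The blinding section rules out blinding all researchers, but its reason covers only participants and intake staff, not data cleaning or the between-arm analyses

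*Protocol article*

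**What the plan says.** All of this is in the protocol article.

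- **Blinding (2.4).** The opening sentence reads: "It is not possible to blind participants or researchers to conditions as all will know whether they will be using the smartphone application or not". The section adds one mitigation, for participants only: "Participants are, however, unaware of the content of the application or the study's hypotheses".
- **Design (2.1).** "All participants start with an individual intake session with a member of the research team in the lab at the university". At that session "participants in the smartphone condition will take a photo of their face (a ‘selfie’) for avatar creation and install the application on their phone". On outcomes: "The outcomes will be assessed using online questionnaires (using Qualtrics software) completed by the participants". Academic results come from the university.
- **Recruitment and randomization (2.3).** "Eligible students are randomly assigned to one of the two conditions on a 1:1 ratio, using block randomization with blocks of 6". Allocation follows the eligibility screen at the start of the intake session, so the staff member present knows the arm from then on.
- **Data management (2.7).** All members of the research team have access to the data. No separation of intake and analysis roles and no masked file is described. Also: "To monitor data quality, attention checks will be incorporated in the questionnaires". The consequence of failing a check is not given.
- **Statistical analyses (2.8).** Aim 2 compares the arms by ANCOVA with the baseline value as covariate and by latent growth curve modelling. Age and gender are added if the arms differ at baseline.
- **Table 2, note b.** App engagement and app experiences are assessed in the smartphone condition only.

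**The concern.** The conclusion in 2.4 is wider than its premise. Knowing who uses the app is unavoidable for the user and for the person who takes part in setting it up. It is not unavoidable for someone working on a data file. As written, the sentence covers researchers without distinction, so a fuller plan that introduced masked cleaning or analysis would have to contradict it.

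The stake is modest but real. Some steps between raw data and result call for judgement: excluding records after failed attention checks, deciding whether the arms differ enough on age or gender to trigger adjustment, and choosing the form of the growth curve. When these are settled with the arms in view, they can drift towards the result the team hopes for. Participants know their condition, so cleaning and analysis are where blinding can still be applied.

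**Working it through.** **Step 1. Who does the stated reason cover?**

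| Role | Must know the arm? | Basis |
|---|---|---|
| Participant | Yes | Uses the app or does not (2.4) |
| Intake staff | Yes | Allocation, selfie and app installation happen in the session (2.1, 2.3) |
| Outcome rater | No such role | Questionnaires are self-completed; academic results are university records (2.1) |
| Data cleaner | No reason given | – |
| Analyst, aim 2 | No reason given | Needs two groups, not their names |
| Analyst, aim 1 | Yes | Usage and experience data exist in one arm only (Table 2, note b) |

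The reason supports the first two rows. Aim 1 is unmasked by its nature. Cleaning and aim 2 are left without a reason.

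**Step 2. Does any figure in the plan change?** No. Masked labels alter neither the sample size, nor the significance level, nor the power.

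**Step 3. What could arm knowledge do? Illustration only.** The documents give no inputs for this, so all of them are assumptions: one outcome, no true effect, k = 2 or 4 defensible specifications, standard normal test statistics with common correlation ρ of 0.7 to 0.9, and an analyst who keeps the one most favourable to the intervention. With φ and Φ the standard normal density and distribution function:

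Favourable-side error = P(max Z > 1.96) = 1 − ∫ φ(u) · Φ((1.96 − √ρ·u)/√(1 − ρ))^k du

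The two-sided rate adds P(max Z < −1.96). With k = 1 the values are 2.5% and 5.0%.

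| k | ρ | Favourable side | Two-sided |
|---|---|---|---|
| 2 | 0.7 | 4.2% | 5.0% |
| 2 | 0.8 | 3.9% | 5.0% |
| 2 | 0.9 | 3.5% | 5.0% |
| 4 | 0.7 | 6.5% | 6.8% |
| 4 | 0.8 | 5.7% | 6.2% |
| 4 | 0.9 | 4.7% | 5.6% |

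The distortion is mainly one of direction: false positives move to the intervention's side, while the two-sided total rises little or not at all.

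**The case against.** **It is only loose wording, and masking of analysts belongs in the analysis plan.** The sentence can be read as describing the people who meet participants, and an article need not say how analysts work. Silence would indeed be no finding. But the text is not silent: it says that researchers cannot be blinded. That statement can be corrected on its face. Equally, how attention-check failures are handled and what form the growth curve takes may be fixed in a document not shown. Their absence from the article is not part of this point.

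**The gain is small.** This stands. Apart from academic results, the effectiveness outcomes are self-reported by participants who know their condition, and masked analysis does nothing about that. Participants' unawareness of the hypotheses helps a little, and there is no staff rater to blind.

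**Masking may leak.** This stands in part. If the people who ran intakes also analyse the data, or if a large difference on future self-identification suggests which arm is which, the mask is imperfect. Team size is not stated.

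A reader might also infer more than the documents support:

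- *That the analysis will be done with open arm labels by those who built the app.* The article gives the team access to the data. It does not say who analyses them, what labels the file carries, or that every member helped to develop the app.
- *That the data are already pseudonymised, so masking costs nothing.* The article does not call the data coded, and aim 1 needs separate handling.
- *That the choice between multiple imputation and full information maximum likelihood is open to preference.* Section 2.8 ties it to the analytical model.
- *That the two-sided error reaches 7.0–8.3% (two specifications) or 9.4–13.0% (four).* Those values belong to an analyst who keeps the largest |Z| in either direction, including results against the app. They do not describe one who favours the intervention.

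**Conclusion.** The point holds in a limited form. Section 2.4 declares impossible something that its own reason does not make impossible. Masked cleaning and masked aim 2 comparisons look feasible from the documents, and they would protect exclusion and modelling decisions. They would not repair self-report bias.

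No sample-size, power or significance figure in the plan is affected. The error rates above rest wholly on the assumed number of specifications, their correlation and the analyst's behaviour. They show the kind of risk and are not an estimate for this trial. This is a cheap improvement to a stated rule, not a flaw that threatens the trial.

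**What to change.** Replace the first sentence of 2.4 with wording such as: *Participants and the staff who run the intake cannot be blinded. Data cleaning and the between-arm analyses for aim 2 are done on a file in which the conditions are labelled A and B.*

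Add to 2.7 or 2.8:

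- An existing team member holds the key. Preferably the analyst has not run intakes.
- App usage and user-experience data, which reveal the arm, stay in a separate file until unmasking.
- Attention-check exclusions, any age or gender adjustment that the baseline rule triggers, and the growth-curve form are decided on the masked file and recorded with a date before the key is opened.

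The cost is a few sentences, one recoded variable and one separate file, with no extra staff. Aim 1 either waits until unmasking or is analysed by another existing team member.

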### Conditions

2.5

#### Intervention

2.5.1

During the intake, participants formulate a monthly- and a yearly goal. The goals can be related to each other, but this is not a requirement. Goal-setting is guided by the researcher to ensure that the goals are specific, measurable, and challenging but attainable, as goals with these characteristics are most likely to have a positive effect on performance (Van Lent and Souverijn, 2020). To this end, goals are determined using the SMART-goal model and Zimmerman's criteria (Ogbeiwi, 2021). Participants also formulate a weekly goal that will facilitate attainment of their monthly goal. During the intake participants independently formulate the first weekly goal, with a reminder of the researcher to consider the SMART-goal model. At the end of each week, participants indicate to which extent they have worked on, and reached, their goal of that week and independently formulate a new weekly goal.

Prior to this RCT, the first version of the FutureU application was extensively user-tested. Semi-structured interviews and focus groups were held among users belonging to the target population as well as experts (i.e., application developers, researchers, and a therapist with experience in smartphone-based interventions). User feedback was processed and used to further improve the application. An overview of module content and core features is provided in Table 1. For screenshots of the application, see Fig. 2.

**Table 1 t0005:** Modules of the intervention.

Week	Module	Aim	Theory	Core features
1	Future self and personality	Stimulating vividness, familiarity and identification with the future self and learn about their own and their future selves' personality	• Exposure to and vividness of the future self increases future orientation (McMichael et al., 2021). • Incremental personality theory: The belief that personality can change over time can reduce problematic behaviors (Yeager, 2017). • People's willingness to change on personality traits in socially desirable ways increases after feedback on their current trait levels (Thielmann and De Vries, 2021).	• Complete personal profile of the future self (e.g., work experience, skills, accomplishments) • Current scores on personality traits with an indication of norm scores • Psychoeducation that personality can change over time • Set scores of personality traits of future self
2	Future self perspective	Practice with distanced perspective taking on problems to make future-oriented choices and increase self-insight with the potential to adjust attitudes and behaviors in favor of the future self	• People make more future-oriented choices: 1) for others (i.e., Solomon's paradox; Grossmann and Kross, 2014) 2) when they have a vivid perception of the future self (McMichael et al., 2021) 3) when they can psychologically or temporally distance themselves from the situation (i.e., Construal level theory; Trope and Liberman, 2003). • Wise reasoning is enhanced with third-person self-reflection (Grossmann et al., 2021)	• Psychoeducation that people make more future-oriented choices when they distance themselves from the situation, and when they think about the long-term consequences • Time travel portal to take future self perspective for giving compliment, advice, and motivation • Participants address themselves in the third-person • Spoken interaction with playback of the recorded messages
3	Goal setting and achievement	Educate about a growth mindset to stimulate goal setting and practice Mental Contrasting and Implementation Intentions to foster goal achievement	• Growth mindset: The belief that people's abilities can develop over time. This mindset aids engagement in thoughts and behaviors to work towards goals (Dweck and Yeager, 2019). • Mental Contrasting and Implementation Intentions (Oettingen and Gollwitzer, 2010): Method in which the desired future is contrasted with the current reality and then reflected upon obstacles in the way of attaining the desired future. Subsequently, a plan is formulated to implement behaviors to overcome obstacles, i.e., implementation intentions, in the format: If situation X, then I will do Y.	• Psychoeducation that abilities can develop over time • Video-clip explaining Mental Contrasting and Implementation Intentions • Practice with Mental Contrasting and Implementation Intentions to work towards goals via filling in a scheme

**Fig. 2 f0010:**
[figure not shown]
FutureU application screenshots of A) connection, B) chat, and C) homescreen and menus.

The main recurrent feature of the application is the interaction with the future self via a chat function (Fig. 2A). During the entire intervention period (i.e., 21 days), participants receive a daily push notification stating that there is a message from their future self. Every other day, participants receive an additional push notification with a general comment of their future self. Every time after opening the application, participants first ‘connect’ with their future self by touching the (virtual) finger of their future self on the blurred screen of their phone. This generates a pulse and unblurs the screen with the avatar of the future self becoming visible (see Fig. 2B). The purpose of this ‘connection mechanic’ is to establish a kinetic connection with the future self and to present participants with an affiliation smile as positive social reinforcement for using the application (Martin et al., 2017). After connection is established, participants enter the chat to interact with their future self as they engage in a scripted conversation (see Fig. 2C). In the chat, the future self provides psychoeducation (both in text and in video-clips), asks questions relating to the participants' perceived future, or provides instructions for the (theory-driven) interaction of that day. The future self also sends images and emojis, and makes jokes to keep the interaction fun. Daily interactions in the application last approximately 5 min or less, as the application favors frequency of contact over length.

#### Control

2.5.2

Participants in the control condition set a monthly- and a yearly goal during the intake, following the same procedure as participants in the intervention condition (see Section 2.5.1 Intervention). Furthermore, participants set a weekly goal that helps them to work towards their monthly goal. As in the intervention condition, the first weekly goal is set independently during the intake with a reminder of the researcher to keep the SMART-goal model in mind when formulating the goal. The other weekly goals are formulated independently by the participant at the end of the weekly questionnaires.

In contrast to the intervention condition, participants do not receive further support for working towards their goals. As the mere act of setting specific, measurable, and challenging goals has been shown to increase positive outcomes (e.g., Van Lent and Souverijn, 2020), this active control condition allows us to examine intervention effects over and above the potential effects of setting goals.

### Measures/instruments

2.6

An overview of the concepts, instruments, and measures at each time point is presented in Table 2.

**Table 2 t0010:** Overview concepts, instruments and assessment time points administered.

Concept	Instrument	#Items	T1	Int.	T2	T3	T4
Future orientation	Future Orientation Scale	15	x		x	x	
Self-defeating behavior	Self-defeating behavior list based on Van Gelder et al. (2015)	16	x	x	x	x	
Goal commitment	Goal Commitment Questionnaire	7	x		x	x	
Weekly goal achievement	Self-developed	3		x	x		
Future self-identification	Based on Hershfield et al. (2009) and Van Gelder et al. (2015)	8	x	x	x	x	
Academic results^a^	University records	–					x
Impulsiveness	Barratt Impulsivity Scale 15 item version	15	x		x	x	
Engagement with application^b^	Smartphone application usage data	–			x		
Smartphone application experiences^b^	Based on mHealth App Usability Questionnaire and the Mobile App Rating Scale	27			x		
Personality	HEXACO-PIR-R100	100	x				
Psychosocial wellbeing	Warwick-Edinburgh Mental Wellbeing scale	14	x	x^c^	x	x	
Self-efficacy	General Self-efficacy Questionnaire	10	x		x	x	
Self-esteem	Rosenberg Self-esteem Scale	10	x		x	x	

a University records will be requested at the end of the academic year (T4).

b Only assessed in the smartphone-based intervention condition.

c The 7-item short version is used for the interim assessments. Int = interim assessments.

#### Primary outcomes

2.6.1

Future orientation will be assessed with the Future Orientation Scale (Steinberg et al., 2009), which measures time perspective, anticipation of future consequences, and planning ahead. The scale consists of 15 items (e.g., “Some people spend very little time thinking about how things might be in the future, but other people spend a lot of time thinking about how things might be in the future.”; α = 0.80).

The self-defeating behavior measure, indicating behaviors with immediate gains and long-term costs, is based on the measure used in Van Gelder et al. (2015). The scale consists of 16 items representing different self-defeating behaviors (e.g., “How often in the past week have you used drugs?”).

The extent to which participants are committed to their year goal will be assessed with the Goal Commitment Questionnaire (Hollenbeck et al., 1989) consisting of 7 items (e.g., “I think this goal is a good goal to shoot for.”; α = 0.71).

Weekly goal achievement will be measured after each week of the intervention, or at parallel time points in the control condition, with 3 items developed for this study: “I often thought about my weekly goal.”, “I have worked towards my weekly goal.”, and “I have achieved my weekly goal.”.

Future self-identification indicates the degree to which people have a clear image of their future self and can identify with their future self. We will assess the vividness with which people can imagine their future self (5 items, e.g., “I find it easy to imagine myself 10-years in the future.”; based on Van Gelder et al., 2015), positive valence towards their future self (1 item, “Indicate how you feel when you think about the future.” answer categories ranging from negative to positive; based on Hershfield et al., 2009), and relatedness with their future self (2 items, e.g., “How connected do you feel with your future self?”; based on Hershfield et al., 2009).

Academic results at the end of the academic year will by requested from university, after student consent.

Impulsiveness is assessed with the Barratt Impulsiveness Scale short form measuring non-planning, motor impulsivity, and attentional impulsivity (Spinella, 2007). The short form consists of 15 items (e.g., “I do things without thinking.”; α = 0.79).

In the smartphone condition, we will additionally assess engagement with the application through usage data and users' experiences with the application immediately after the intervention through a questionnaire. User experience measures (27 items in total) include ease of use (e.g., “The app was easy to use.”), satisfaction (“I am satisfied with the app.”), and acceptability (e.g., “I would use the app again.”) of the application. They are based on the subscale Ease of use and satisfaction of the mHealth App Usability Questionnaire (Zhou et al., 2019) and the subscale Functionality of the Mobile App Rating Scale (Stoyanov et al., 2015).

